### Interim analyses {21b}

No interim analyses will be performed, but the final number of randomised people needed to reach the target sample size will be checked before closure of trial enrolment, to ensure adequate power in the analysis of the primary outcome.

### Methods for additional analyses (e.g. subgroup analyses) {20b}

People with COPD and ILD will be analysed separately. If the projected sample size is not reached, all randomised people can be analysed as a secondary analysis, which will be detailed in the SAP.

### Methods in analysis to handle protocol non-adherence and any statistical methods to handle missing data {20c}

Missing values of predictors and confounders will be imputed by multiple imputation approaches.

Any trial deviations, including reportion deviations, will be specified in the SAP before each analysis.

### Plans to give access to the full protocol, participant level-data and statistical code {31c}

All upcoming manuscripts will be published with open access.

Data cannot be made freely available as they are subject to privacy in accordance with the Swedish Public Access to Information and Secrecy Act. Requests for data can be sent to the corresponding author and are available after approval from the Swedish Ethical Board ([contact]) for researchers who meet the criteria for access to confidential data. Authors may be contacted to aid with the data access from the Ethical Board.

## Oversight and monitoring

### Composition of the coordinating centre and trial steering committee {5d}

The steering committee, including all co-authors of the protocol paper, is responsible for creating the protocol and standard operating procedures, and for follow-up meetings during the trial. The participants are all PIs and/or researchers with a special interest in the area. The research unit Clinical Studies Sweden Forum South is the coordinating centre and is responsible for agreements, start meetings support, and monitoring of the trial sites. A representative from ResMed is participating in all steering group meetings to support practical discussion about the high-flow device.

### Composition of the data monitoring committee, its role and reporting structure {21a}

The clinical investigation will be monitored by an independent monitor before the clinical investigation begins, during the clinical investigation conduct, and after the clinical investigation has been completed, to ensure that the clinical investigation is carried out according to the clinical investigation plan (CIP) and that data are collected, documented, and reported according to SS–EN ISO 14155:2020 and applicable ethical and regulatory requirements. Monitoring is performed as per the investigation’s risk analysis and monitoring plan and is intended to ensure that the subject’s rights, safety, and well-being are met as well as data in the CRF are complete, correct, and consistent with the source data.

### Adverse event reporting and harms {22}

As the LUMIS HFT device is an approved and CE-marked product, only unexpected events will be reported. According to the manufacturer, drying of the nose, mouth, or throat, nosebleed, bloating, and skin rashes may arise during treatment, but no serious adverse events have been recorded with HFOT in previous studies [13–15]. However, people should be asked to report unusual chest pain, severe headache, or increased breathlessness to their prescribing physician. An acute upper respiratory tract infection may require temporary discontinuation of treatment. Known side effects related to the trial treatments or underlying diseases will not be reported in the e-CRF.

Adverse events will be assessed at 1-week telephone follow-up, from patient register data on hospitalisations, from patient questionnaires at 3 and 12 months, and at the patient’s clinical visits according to clinical routines.

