## Objectives {7}

The overall objective of this trial is to improve the evidence-based treatment in people with chronic respiratory failure due to COPD or ILD.

The primary objective is to test the effect of added HFOT as compared to usual LFOT on time to first hospitalisation or death during 1 year in people with oxygen-dependent chronic respiratory failure (CRF) due to COPD.

The secondary objectives are as follows:To evaluate treatment effects on other outcomes including respiratory symptoms, HRQL measured via validated questionnaires, and health-economics, and to explore the effects of HFOT in people with CRF due to ILDTo assess adverse effects of HFOT compared with LFOT

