### Criteria for discontinuing or modifying allocated interventions {11b}

Participants will be withdrawn if the trial treatment is judged to be harmful or carry unacceptable risk for harm, or at any time at the discretion of the participant. The trial treatment can be changed or discontinued at the discretion of the responsible physician or participant, which is not a reason for withdrawal from the trial.

Trial participation is completely voluntary and participants who wish to do so can withdraw at any time. Participants who want to withdraw will be asked which trial procedures they want to withdraw from, and whether they consent to be included in parts of the follow-up, including the registry-based endpoints.

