### Outcomes {12}

The primary outcome is time to first hospitalisation or death from all causes during 1 year after randomisation in people with COPD (at 1 year, assessed using nationwide registries).

Secondary outcomes are as follows:Time to first all-cause hospitalisation or all-cause death in people with ILD (at 1 year after randomisation, assessed using nationwide registries).Rate of hospitalisations or death from all causes (at 1 year).Hospitalisation rate from all causes (1-year and long-term).Hospitalisation rate from respiratory disease (1-year and long-term).Hospitalisation rate from cardiovascular disease (1-year and long-term).Number of hospitalised days (all-cause/respiratory disease/cardiovascular disease) (at 1 year and long-term).Number of admissions to intensive care unit (ICU) (at 1 year and long-term).Number of days in ICU care (at 1 year and long-term).The mortality rate from all causes (at 1 year and long-term).The mortality rate from respiratory disease (at 1 year and long term). The mortality rate from cardiovascular disease (at 1 year and long-term).Time to first exacerbation after randomisation, defined as time to first dispensed antibiotics and/or oral corticosteroids, emergency department visit, or hospitalisation for exacerbation (at 1 year).Number of exacerbations of all severity (at 1 year).Incidence of cardiovascular disease (at 1 year and long-term).Need for home mechanical ventilation (at 1 year and long-term).Rate of LFOT withdrawal (at 1 year and long-term).Safety and tolerability (adverse events at 3 and 12 months).Cost-effectiveness (at 1 year and long-term).HRQL (at 3 and 12 months).Symptoms (dyspnea, cough, phlegm, upper airway symptoms, fatigue, including nighttime symptoms, sleep) (at 3 and 12 months).Factors associated with the net clinical benefit of the HFOT, including the daily usage time.Patients’ perceptions of oxygen therapy and related factors.Adverse events as safety endpoints.

The secondary outcomes will be evaluated in the following populations: (1) people with COPD; (2) people with ILD; and (3) all people. All analyses will be performed primarily by randomised treatment group (intention to treat; ITT), and secondarily by treatment used (per protocol; PP).

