## Data collection and management

### Plans for assessment and collection of outcomes {18a}

Outcome data will be obtained from patient questionnaires at baseline, 3 and 12 months, from Swedevox, from trial specific data entered in the eCRF by the PIs, and from national registries. In centres using the remote home-monitoring system AirView, data on HFOT utilisation will be used.

The questionnaires will include questions on oxygen and HFOT usage, patient preference for continuing the treatment, utilisation of primary care and domestic service, adverse events, and the number of exacerbations since the start of the trial. Symptoms included in the questionnaires are breathlessness using a modified Dyspnoea Exertion Scale (DES) [34] and the Dyspnoea-12 questionnaire [35, 36], cough and phlegm assessed by relevant items in the COPD Assessment Test (CAT) [37], sleep complaints using a modified Basic Nordic Sleep Questionnaire (BNSQ) [38], nasal symptoms, and subjective perception of change in health status assessed with a modified Global Impression of Change (GIC) scale [39]. Physical activity is reported for the previous month using a modified Grimby activity questionnaire [40, 41], and HRQL is evaluated using the CAT [37] and EuroQol Five Dimensions Five Levels (EQ5D-5D-5L) [42].

Data from Swedevox will be used for characterising the people and their oxygen treatment, and for assessment of rate and reason of LFOT withdrawal during follow-up. The ventilator arm of the Swedevox registry will be used to assess the incidence of long-term home mechanical ventilator usage.

If applicable, data on HFOT utilisation will be collected from centres using Airview at 1 week, 3 and 12 months on: average usage time, daytime and nighttime use, days of use, and days of use ≥ 4 h/24 h. Data on oxygen flow and HFOT settings will be collected from staff-reported questionnaires at 3 and 12 months.

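### Known side effects are kept out of the eCRF although a between-arm comparison of adverse effects is promised, and follow-up after withdrawal for harm is left unclear

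*Protocol article*

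**What the plan says.** Objectives {7} includes, as a secondary objective, to "assess adverse effects of HFOT compared with LFOT". Outcomes {12} lists "Safety and tolerability (adverse events at 3 and 12 months") and, as a further item, adverse events as safety endpoints.

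Adverse event reporting and harms {22} says that, because the device is CE-marked, "only unexpected events will be reported". It cites the manufacturer for the expected effects: "drying of the nose, mouth, or throat, nosebleed, bloating, and skin rashes may arise during treatment". It then adds: "Known side effects related to the trial treatments or underlying diseases will not be reported in the e-CRF". Its next paragraph names the sources: "Adverse events will be assessed at 1-week telephone follow-up, from patient register data on hospitalisations, from patient questionnaires at 3 and 12 months", and also routine clinical visits.

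Plans for assessment and collection of outcomes {18a} confirms that the patient questionnaires ask about "adverse events, and the number of exacerbations since the start of the trial", and also about nasal symptoms and sleep.

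On withdrawal, Criteria for discontinuing or modifying allocated interventions {11b} says: "Participants will be withdrawn if the trial treatment is judged to be harmful or carry unacceptable risk for harm", or at the participant's own wish. The following sentence says that changing or stopping the trial treatment is not a reason for withdrawal from the trial. The offer of partial or registry-only follow-up, there and in Plans to promote participant retention {18b}, is addressed to people who want to withdraw.

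**The concern.** Limiting expedited reporting to unexpected events is a regulatory matter and is not at issue. The eCRF sentence goes further, because it limits what enters the trial dataset. The effects it removes are the expected device effects, which a comparison of HFOT with LFOT would look at first. Staff are asked to assess adverse events at the 1-week call and at visits, but the article names no place where a known effect heard there is kept. Early intolerance would then first be recorded at 3 months, by recall, from those still alive and willing to reply.

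The rule also covers events of the underlying disease. Unblinded staff must therefore judge whether, say, increased breathlessness is known and left out, or unexpected and entered.

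The withdrawal wording raises a second question. A site could read it as ending all follow-up for a participant whose treatment is judged harmful. If questionnaires stopped for those people, the missing safety data would be related to harm itself.

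**Working it through.** The plan gives no figure for adverse-event capture, questionnaire return, mortality alone or withdrawal for harm, so there is no stated number to reproduce. The sample size of 270 does not enter this point. The check is a reading of the sections side by side, with two illustrations on assumed values.

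**1. Where a known effect that does not lead to admission can be recorded** (for example, a nosebleed managed at home)

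- 1-week call: assessed by staff, barred from the eCRF, no other destination named.
- Clinical visits: the same.
- Staff forms at 3 and 12 months: described in {11c} and {18a} as covering HFOT use, oxygen flow and device settings; adverse events are not mentioned.
- Registry hospitalisations: complete without any reply, and they cover people who later die, but they do not hold such an event.
- Patient questionnaires at 3 and 12 months: cover adverse events, nasal symptoms and sleep; posted by a unit separate from the sponsor (Confidentiality {27}).

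Only the last route remains, and participants know their treatment (Who will be blinded {17a}).

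**2. Coverage of that route**

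Assumptions, not in the documents: 1-year mortality m of 20% to 40%; 80% of survivors return the form; constant mortality hazard.

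- 12 months: (1 − m) × 0.80. This gives 0.80 × 0.80 = 0.64 and 0.60 × 0.80 = 0.48.
- 3 months: (1 − m)^(3/12) × 0.80. This gives 0.80^0.25 × 0.80 = 0.946 × 0.80 = 0.76 and 0.60^0.25 × 0.80 = 0.880 × 0.80 = 0.70.

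The 12-month figure counts a death as a missing form. Some of those people will have replied at 3 months.

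**3. Withdrawal for harm**

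- {11b}, first sentence: the participant, not only the treatment, is withdrawn when treatment is judged harmful.
- {11b}, second sentence, and {18b}: stopping treatment is not a reason for withdrawal, and {18b} adds that such people are analysed as randomised.
- Statistical methods {20a}: the ITT population leaves out only those who withdrew consent to be included in the outcome analyses. A person withdrawn for harm has not done that and so remains in.
- Continued follow-up: described only for those who want to withdraw. Nothing says whether questionnaires go on after withdrawal for harm.

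**4. What informative loss of questionnaires could do to the safety comparison**

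Assume a true side-effect risk p in the HFOT arm, and that a fraction w of that arm is withdrawn for harm, all having had the effect and none returning a form. The observed risk is (p − w)/(1 − w).

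- p = 20%, w = 5%: 0.15/0.95 = 15.8%.
- p = 20%, w = 10%: 0.10/0.90 = 11.1%.
- p = 30%, w = 5%: 0.25/0.95 = 26.3%.
- p = 30%, w = 10%: 0.20/0.90 = 22.2%.

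This is a worst case. If questionnaires continue after withdrawal, this loss does not arise.

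**The case against.** The strongest reply is that the eCRF is one route among several. Both arms receive questionnaires at exactly the two time points named for the safety outcome, and patient report is a legitimate way to measure tolerability. Registry hospitalisations need no reply. The article also condenses a clinical investigation plan and refers to a data management plan, neither shown, where recording details may sit. This stands to the extent that the objective does not go unanswered. It does not remove the point about the eCRF, because the article states a rule there and is not merely silent.

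Four stronger readings are tempting, and the documents do not support them.

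- A reader might infer that the adverse-effect objective cannot be met. The questionnaires and registries rule that out.
- A reader might infer that the gaps favour HFOT. The rule applies to both arms, and Background and rationale {6a} attributes dryness and other airway effects to LFOT, so under-recording could equally hide a benefit of HFOT.
- A reader might infer that the reasons pilot participants stopped are the effects barred from the eCRF. The Discussion gives trouble sleeping because of discomfort and noise as the commonest reasons. Those are not on the manufacturer's list in {22}, and the questionnaires cover sleep.
- A reader might infer bias in the primary hazard ratio. The ITT definition in {20a} keeps people withdrawn for harm, and the primary outcome comes from registries. Nothing says they are censored or dropped.

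**Conclusion.** The point holds, at moderate severity. The eCRF rule sits badly with the promised comparison: known effects without admission rest on unblinded recall at 3 and 12 months, although staff contacts take place earlier. On the assumed mortality and return rates, that source would cover about 70–76% of those randomised at 3 months and 48–64% at 12 months. These ranges move directly with the assumptions, and the direction of any bias is not established.

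The withdrawal wording is internally inconsistent. The ITT definition protects the primary analysis. What is left open is continued follow-up, the questionnaires above all, for people withdrawn because of harm. The risk figures in the last working step show the possible size of that loss if it occurred in one arm; the documents give no withdrawal rate.

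**What to change.** 1. Replace the eCRF sentence in {22} with a short form, identical in both arms, completed at the 1-week call and added to the existing staff forms at 3 and 12 months. It should list the known effects already named in {22}, and the date of and reason for any stopping of treatment. Expedited reporting can stay limited to unexpected events.

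2. Reconcile the first two sentences of {11b} with {18b} and {20a}, so that stopping the trial treatment for any reason, including judged harm, does not end registry or questionnaire follow-up unless the participant withdraws consent for it. This concerns follow-up only; no clinical rule on stopping treatment is changed or proposed.

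The cost is a few minutes per contact, an addition to the eCRF and a sentence or two in the protocol. Recruitment is under way, so the new form would supply data only from its introduction onward. The report should say so and show how many participants it covers in each arm.

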### Frequency and plans for auditing trial conduct {23}

Auditing of the trial takes place at the incentive of the Swedish Medical Product Agency (MPA). The MPA may suspend or prematurely terminate the clinical investigation at the applicable investigation sites.

### Plans for communicating important protocol amendments to relevant parties (e.g. trial participants, ethical committees) {25}

Amendments to the CIP will be agreed upon between the coordinating investigator and the Sponsor. Substantial modifications must be approved by the Swedish Ethical Review Authority and/or the Swedish Medical Products Agency (as applicable) before implementation. Investigator(s) are not allowed to deviate from the CIP except if it is for the protection of the subject’s rights, safety, or well-being under emergency circumstances. All such deviations shall be documented and reported to the Sponsor, the Swedish Medical Products Agency and/or the Swedish Ethical Review Authority (as applicable) as soon as possible. All deviations shall be documented with an explanation and reported to the Sponsor. Deviations will be reviewed by the Sponsor and reported to the appropriate regulatory bodies as required.

## Dissemination plans {31a}

The project will result in several publications in peer-reviewed international journals on: (1) trial design; (2) primary and main secondary outcomes; (3) health economic analysis; (4) additional secondary outcomes including in people with ILD; (5) correlational analyses of predictors of net clinical benefit; (6) systematic review and meta-analysis with all available data in this field; and (7) long-term registry follow-up. The results of the study are expected to be implemented in national and international clinical guidelines on home oxygen therapy.

## Discussion

This is the largest multi-centre RCT to assess the benefits of HFOT to date, and the first to include people with ILD. The study will have power to assess mortality and hospitalisation as a primary outcome and health-economics as a secondary outcome. Although LFOT is an established treatment that improves survival in people with chronic respiratory failure and severe hypoxemia [1, 2], the risk of hospitalisation and death in people with LFOT is very high [5, 8], and it is of great importance to assess interventions that may improve the prognosis. In addition, people with LFOT experience a high burden of local side effects with an impact on their HRQL [6], and HFOT could potentially decrease these problems.

The trial started with a pilot phase at the centres in Örebro and Karlskrona, to evaluate feasibility and therapy adherence. Early challenges were identified, particularly related to patient adherence due to device-related discomfort, as the majority of people randomised to HFOT were non-adherent and chose to end the treatment. The most common reasons were difficulties in sleeping due to discomfort and noise from the device. As a consequence, adjustments in initial flow settings and patient education strategies were made. The standard procedure was changed to aim for an initial lower oxygen flow of 20 L/min to get used to the high oxygen flow and to preferably use a somewhat larger nasal cannula to reduce the sound from the gas flow. In addition, a notification that it may take a couple of weeks to adjust to the new treatment was added to the standard information at the baseline visit.

Until end of spring 2025, start meetings have been held at the remaining sites, and the study is now recruiting at all ten sites.

## Trial status

The study is ongoing, present protocol version nr 1.1, dated 21 of February 2025. First recruitment was performed on 10th of June 2024. The study is expected to be finished earliest in 2028.

## Data Availability

The primary investigator and the project statistician will have full access to the final trial dataset. Data will not be shared with other investigators outside the sponsor Region Skåne unless preceded by a contractual agreement.

## Abbreviations

BMI: Body mass index
BNSQ: Basic Nordic Sleep Questionnaire
CAT: Chronic Obstructive Pulmonary Disease Assessment Test
CIP: Clinical investigation plan
COPD: Chronic obstructive pulmonary disease
CPAP: Continuous positive airway pressure
CRF: Chronic respiratory failure
DES: Dyspnoea Exertion Scale
DMP: Data management plan
eCRF: Electronic case report file
EQ-5D-5L: EuroQol-5 dimension- 5 levels
HFOT: High-flow oxygen therapy
HILOT: Effect of HIgh-flow Therapy in Long-term Oxygen Therapy
HRQL: Health-related quality of life
ILD: Interstitial lung disease
ITT: Intention to treat
LFOT: Low-flow oxygen therapy
MPA: Medical product agency
PI: Primary investigator
PP: Per protocol
OHS: Obesity hypoventilation syndrome
OSA: Obstructive sleep apnoea
RCT: Randomised controlled trial
R-RCT: Registry-based randomised clinical trial
SAP: Statistical analysis plan
